### 2.11. Data monitoring

Data for this clinical study will be collected using e-CRF. Further, we will ensure that the data on the e-CRF conforms with the hand-written source document that and they are accurate, complete, readable, and timely. Only the researcher or a permitted person is permitted to edit the e-CRF and source documents.

The researchers should keep and secure the data and records related to the conduct of the clinical study in a safe place and preserve it for three years from the date of completion of the clinical study and the date of discontinuation. After completing the preparation of the result report, the clinical research-related documents should be handed over to the person in charge of storage. If the researcher intends to discard or move the clinical research-related records, the sponsor should be informed in advance.

Monitoring will be carried out to protect the rights and welfare of subjects; to verify the accuracy, completeness, and verifiability of data by comparing reported clinical research data with source documents; and to confirm whether clinical research is performed according to the approved protocol and management standards. Olive Healthcare Co. Ltd. (Seoul, Republic of Korea), a consignment institution for clinical research, monitors clinical research through regular institutional visits and phone calls, evaluates clinical research progress, and confirms whether researchers perform their duties according to research plans and regulations. During the institutional visit, the monitoring officer will check the archiving of original source documents, e-CRF, drug management records, and research-related data and discuss any discrepancies or problems with the clinical study records with the investigator.

### 2.12. Adverse events

An adverse event refers to all harmful and unintended signs (including signs and abnormalities in laboratory test results), symptoms, or diseases that occurred in subjects who have received the tested food. These adverse reactions do not necessarily have a causal relationship with the tested food and might include abnormal test results, clinically significant symptoms or signs, changes in physical examination results, hypersensitivity, and progression or worsening of existing diseases.

All serious adverse events occurring during the clinical study period, whether related to the tested food or not, should be reported to the sponsor within 24 hour of the investigator’s awareness, regardless of administration. Adverse reactions occurring up to 28 days after the last administration of the tested food, after the end of the clinical study, should be reported only if they are serious and related to the tested food.

If a suspected unexpected serious adverse reaction (SUSAR) has occurred, the principal investigator should report it to the IRB, to decide whether the study should be continued or discontinued, and report it to the Minister of Food and Drug Safety promptly within the period specified in each of the following items through the sponsor:

- SUSAR that causes death or threatens life must be reported to the Minister of Food and Drug Safety as soon as possible through telephone, fax, or documents within seven days of the first report or knowledge of the sponsor, and a complete report additional reports must be made within 15 days of the date of first knowledge.- All other SUSAR should be reported as soon as possible within 15 days from the date the sponsor receives or becomes aware of the fact.

### 2.13. Concomitant drugs and treatments

#### 2.13..1. Acceptable drugs or treatments.

The drugs listed below are approved for concomitant use at the discretion of the investigator.

- Drugs that have been regularly administered within 4 weeks prior to visit 1- It is considered that it will not affect the interpretation of the results of this clinical study among the concomitant drugs that the subject has been taking before participating in this clinical study.- Drugs used temporarily for the treatment of other diseases or adverse reactions

When administering all concomitant drugs, information about the drug (product name, administration purpose, administration dose, administration period) should be recorded in detail in the subject’s e-CRF.

#### 2.13..2. Prohibited drugs or treatments.

- Administration of growth hormone drugs and injections- Food oriental medicine related to height growth food and growth promotion- The case of administering other foods and drugs is defined as a treatment change, which can be determined by the attending physician. However, temporarily increasing the dose of the currently administered drug is not a reason for a change in treatment.

## 3. Discussion

With the development of science and technology, the number of children with growth difficulties due to hunger has decreased in many developed countries.^[15]^ According to a survey,^[16]^ the ratio of households to ensure food safety (i.e., the proportion of those who answered that the whole family ate a sufficient amount and type of food as desired) has shown a gradual increase over the past 10 years, confirming that the quality of nutritional intake has improved compared to the previous status. However, for the majority of parents, the growth of their children is a major concern, and parents are putting a lot of effort and investment into achieving better growth outcomes. According to a survey on the use of Korean medicine and Korean herbal medicine consumption in Korea in 2020,^[17]^ the interest in growth is high enough that 24.4% of children under the age of 19 used Korean medicine for the purpose of growth.

In practice, short stature is defined as 2 standard deviations below the average height of children of the same sex and age. However, even children who fall within the normal range desire to have larger heights, so they often visit medical institutions or find various ways to promote growth.^[18]^ Further, the average height continues to increase due to the improvements in eating habits and quality of life. However, a psychological burden might be imposed and persist into adulthood if growth does not happen smoothly according to the social atmosphere that favors taller heights.

Research on materials that can promote growth in such atmospheres is continuously being conducted. In particular, several experimental studies have been conducted on the growth effect of herbal medicines on bone growth, including single drugs such as astragalus and deer antlers and complex drugs containing Poria cocos or Dioscorea Rhizoma.^[19]^

Deer antlers are cut and dried young male antlers of Cervus nippon Temminck (梅花鹿), Cervus elaphus Linne (馬鹿), or Cervus canadensis Erxleben (大鹿) and are the fastest growing part of the animal tissues. Insulin-like growth factor-1 (IGF-1), which promotes bone growth, is produced in growing deer antlers, and IGF-1 is known to play an important role in the metabolism of osteoblasts that grow bones. Deer antler is originally a representative tonifying yang medicine (補陽藥) and has effects such as tonifying kidney yang (補腎阳), replenishing essence and blood (益精血), and strengthening muscle and bone (强筋骨).^[20]^ Kidney yang (腎阳) activates overall physiological function by warming the organs of the human body. Based on the efficacy of antlers, this clinical study is designed to prove the safety and effectiveness of promoting height and growth in children and adolescents.

The primary outcome item, height change, is the most intuitive item for judging a child’s growth. Generally, children older than 2 years whose height velocity is less than 4 cm/year should be monitored carefully for chronic nutritional deficits or other causes of short stature because at least 95% of children grow faster than 4 cm/year.^[21]^ However, since each subject’s current growth status is different, items such as SDS and height percentile are selected as secondary outcome measurements. In addition, since length growth is not the only growth indicator, weight growth-related indicators such as weight, waist circumference, and hip circumference will be also measured. Further, to determine the effect on future growth, bone age and predicted adult height will be used for growth prediction.

Among the secondary outcome items, hormone-related items including IGF-1, IGFBP-3, and estradiol levels will be also evaluated. IGF and IGFBP-3 are major indicators for measuring the effect of growth hormones on peripheral tissues and are frequently used indicators in studies confirming the effect of growth. IGF-1 is a hormone that functions as a major mediator of GH-stimulated somatic growth, as well as a mediator of GH-independent anabolic responses in many cells and tissues.^[22]^ IGF-1 is synthesized in the liver and is secreted into the blood under the control of GH. Further, a major function of IGFBP is to transport IGF, which controls access to the extravascular space, as well as tissue localization and distribution. IGFBP-3 is the most abundant form in plasma, with the highest affinity for IGF-1, and is in a saturated state.^[23]^ Estradiol is an estrogen steroid hormone and a major female sex hormone. Additionally, it has important effects on many other tissues, including fat, skin, liver, and the brain, especially estradiol, which has a profound effect on bone. Further, lack of estradiol would result in delayed epiphyseal.^[24]^ By examining the level of estradiol, we also wanted to confirm that antler extract does not interfere with female hormone levels and causes precocious puberty or other hormone-related symptoms.

A limitation of this study is that the stratification will proceed after receiving the study participants without considering the number of participants by age or gender. Further, as the study progresses, the age or sex might influence and bias the results. However, this conforms with the aim of this study, which is to examine the growth effect of antler extract for all children aged 3 to 12 years. Accordingly, additional research should be conducted to compare the growth effects according to age or sex.

In addition, it can be considered that food intake, which should be considered in many growth-related studies, will also affect the growth effect of deer antler extract. Since it was essentially impossible to control the diet and amount of food of the study participants, to reduce the deviation as much as possible, the test was conducted with a lifestyle test paper for children and adolescents, and a dietary questionnaire was distributed to record food intake while eating the study food. For a more precise study, it is necessary in the future to conduct a more detailed stratification classification, by considering the diet and meal amount based on the recorded data, and compare the results before and after taking the test drug in each stratified group.

The human body test protocol and case record file for this study were developed through the approval process several times under the management of the Institutional Review Board of Kyung Hee University Korean Medicine Hospital. Further, additional revision and supplementation processes might be performed for various reasons that might occur during the human application test. It is expected that significant results for the efficacy and safety of antler extract for pediatric height growth can be obtained through human application studies using this protocol.

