### 2.4. Sample size

The expected difference in height change was set to 0.45 cm.^[14]^ Based on this, the difference between groups was tripled and set at 1.35 cm. The standard deviation (σ) was set to 2.0, which is the standard for growth disorders (less than −2.0 standard deviation from the average of children of the same age and sex). Accordingly, the sample size was calculated using a 2-tailed 5% significance level, 80% power, and a 1:1 allocation. Accordingly, the required number of subjects per group is 35 and the total number of enrolled subjects is 100 (50 in each group), allowing for a 30% withdrawal rate.

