### 2.10. Statistical analyses

In this study, analysis will be performed by defining the analysis group as safety, full analysis set (FAS), and per-protocol set analysis. The safety analysis group will be defined as all subjects who have been randomized and who have consumed at least 1 study food and will be evaluated for safety. The FAS analysis group refers to subjects for whom data on primary outcomes can be obtained among those who have taken research food at least once. The per protocol set analysis group includes subjects who have completed the study without serious violations (violation of inclusion and exclusion criteria, use of concomitant medications that are not permitted, and medication adherence less than 70%) according to the research protocol among subjects included in the FAS analysis group. If missing data occurs during FAS analysis or if a subject drops out before the clinical study is terminated, data analysis will be performed with the most recently obtained data as if it were obtained at that time (Last Observation Carried Forward Method).

Statistical analysis is intended to test whether there is a statistical difference between the test and control groups. Therefore, the mean, standard deviation, median, minimum, and maximum values of the outcome measurements will be calculated, and comparisons between the groups will be performed using a 2-sample t-test (Wilcoxon’s rank sum test when the assumption of normality distribution is not satisfied). For laboratory tests and vital sign results, a paired t-test will be used to analyze whether there will be a difference in the amount of change within the group at the end of administration of the test substance compared with before treatment (screening). Further, PAH will be sub-analyzed according to calculation methods such as the VunoMed, TW, and growth chart methods. Additionally, covariate analysis (analysis of covariance; ANCOVA) with stratification as a covariate and subgroup analysis for each stratification will be conducted.

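### Estradiol is measured to confirm no hormonal interference, but every planned analysis tests for a difference and the sample was sized on height alone

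*Protocol article*

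**What the plan says.** - **Aim for estradiol (3. Discussion).** The reason given for examining it is that "we also wanted to confirm that antler extract does not interfere with female hormone levels". The same sentence goes on to precocious puberty and other hormone-related symptoms.
- **Wider aim (3. Discussion).** "this clinical study is designed to prove the safety and effectiveness of promoting height and growth in children and adolescents".
- **Purpose of the analysis (2.10).** "Statistical analysis is intended to test whether there is a statistical difference between the test and control groups".
- **Tests (2.10).** Between groups, "comparisons between the groups will be performed using a 2-sample t-test", with a rank-sum test if normality fails. For laboratory tests and vital signs, "a paired t-test will be used to analyze whether there will be a difference in the amount of change within the group". The section also plans ANCOVA with stratification as a covariate and a subgroup analysis for each stratum.
- **Strata (2.8, Table 1).** There are four, each of a single sex. Group 2 is the older girls, aged 9 to 12.
- **Sample size (2.4).** It is built on height change: "the difference between groups was tripled and set at 1.35 cm" and "The standard deviation (σ) was set to 2.0". This gives 35 per group, raised to 50 per group for 30% withdrawal.
- **Estradiol measurement (2.9.2.6).** Blood is taken at baseline, 6 and 12 weeks. Here estradiol is listed among four hormones that indicate growth status, which is a different role from the safety role in the Discussion.

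**The concern.** The Discussion sets out to show that something is absent, while the analysis section sets out to detect that it is present. Failure to reject the hypothesis of no difference is compatible with no effect, and equally with an effect too small for the trial to see. The article states no margin and no interval-based rule that would turn the estradiol data into evidence for absence, and it gives the purpose of the analysis in a form that points the other way.

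The paired test adds a second difficulty. The notes to Figure 2 group estradiol with the laboratory tests, so the test may well be applied to it. A change within one arm over 12 weeks of childhood mixes any extract effect with ordinary maturation, and only the comparison with placebo separates the two. A significant paired result would not show interference, and a non-significant one would not exclude it.

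At stake is what the trial may say about hormonal safety in children aged 3 to 12.

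**Working it through.** **1. The plan's own figure.** Inputs from 2.4: difference 1.35 cm, SD 2.0, and "the sample size was calculated using a 2-tailed 5% significance level, 80% power, and a 1:1 allocation".

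n per arm = 2 × [2.0 × (1.960 + 0.842) / 1.35]² = 34.45, rounded up to 35. Then 35 / (1 − 0.30) = 50 per arm, 100 in total. The stated size reproduces. No estradiol quantity enters it.

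**2. Precision for estradiol.** The article gives no estradiol SD, so results are in units of the SD of estradiol change, assumed common to both arms.

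95% CI half-width = t(0.975, 2n − 2) × √(2/n). The detectable difference is for a two-sided 5% t-test with 80% power.

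| Children per arm | Source | CI half-width | Detectable difference |
|---|---|---|---|
| 50 | all enrolled | 0.40 SD | 0.57 SD |
| 35 | after 30% withdrawal | 0.48 SD | 0.68 SD |
| 12 | one stratum, four equal strata assumed, no withdrawal (50/4 = 12.5) | 0.85 SD | 1.2 SD |
| 9 | one stratum, equal strata assumed, after withdrawal (35/4 = 8.75) | 1.0 SD | 1.4 SD |

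The equal split is an assumption. The Discussion says that numbers by age and sex are not controlled, so a stratum may be smaller or larger than this.

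**3. How often a real shift would be non-significant.** Normal approximation: 1 − Φ(d / √(2/n) − 1.960), with d the true difference in SD units.

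- d = 0.3: 76% with 35 per arm, 68% with 50.
- d = 0.4: for n = 35, 0.4 / 0.239 = 1.673, and 1 − Φ(−0.287) = 61%. For n = 50, 0.4 / 0.2 = 2.0, and 1 − Φ(0.04) = 48%.
- d = 0.5: 45% with 35 per arm, 30% with 50.

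**4. What a margin-based conclusion could support.** Assume a true difference of zero, one-sided alpha 0.025 and 80% power. The smallest margin is (1.960 + 0.842) × √(2/n) = 0.67 SD with 35 per arm and 0.56 SD with 50. For two-sided equivalence (two one-sided 5% tests) it is (1.645 + 1.282) × √(2/n) = 0.70 SD and 0.59 SD. The documents give no margin. As an illustration, an assumed non-inferiority margin of 0.3 SD would need 175 evaluable children per arm, and one of 0.5 SD would need 63.

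**5. Passages side by side.** The Discussion asks for confirmation of no interference. Section 2.10 offers a two-sample comparison, a paired comparison, a stratum-adjusted comparison and stratum subgroups, and states their purpose as testing for a difference. The ANCOVA is the most useful of these, since it yields an adjusted between-group estimate from which an interval follows. The subgroups look in the right place, but with the widest intervals.

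**The case against.** The best case against the point is that it leans on one verb. The sentence is a remark on rationale in the Discussion, about one of many secondary outcomes, and no formal safety hypothesis or decision rule is attached to it. Safety does not rest on estradiol alone: 2.10 defines a safety set, and 2.12 counts laboratory abnormalities as adverse events and sets out reporting. Confidence intervals and margins for a secondary laboratory outcome often sit in a full protocol or SAP that is not shown. Wide intervals are also common to every secondary outcome in a trial of 100 children.

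Much of this stands, and it limits the weight of the point. Two stronger readings should be set aside:

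- **That the t-tests are the only analyses, so sexes and ages are merely pooled and an effect in older girls would be diluted out of sight.** The article does not support this. Section 2.10 plans stratum-adjusted ANCOVA and an analysis within each stratum, and Table 1 makes girls aged 9 to 12 a stratum of their own. The weakness there is precision.
- **That the trial will treat a non-significant p-value as proof of safety.** No passage says so. It is an inference from an aim of confirmation paired only with difference tests.

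The mismatch remains. It is more than a detail left to another document, because the article itself states both the aim and an analysis purpose that cannot deliver it.

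**Conclusion.** The point holds as a mismatch between aim and analysis, and is worth correcting because the correction is cheap. No analysis described in the article, used as the difference test it is stated to be, can confirm that the extract leaves estradiol unaffected. After a null result with 35 to 50 per arm, the data could still be compatible with group differences of up to roughly half an SD. Within a stratum of about 12 per arm the interval is about ±0.85 SD.

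The figures assume a common SD, approximate normality and, for strata, an equal split. Estradiol may be skewed in this age range, and covariate adjustment may tighten the overall interval somewhat, so the SD-unit values are indicative. The logical conclusion does not depend on them. The height sample size reproduces and is not in question here.

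**What to change.** 1. Reword the aim in the Discussion from confirming no interference to estimating the effect of the extract on estradiol.
2. Report the between-group difference in estradiol change with a 95% confidence interval: overall from the stratum-adjusted ANCOVA already planned, and separately for girls and boys. If the data are skewed, use a scale or method that still yields an interval, since a rank-sum p-value alone would not serve.
3. State that a non-significant result is not evidence of no effect, and that the within-group paired test is descriptive for estradiol.
4. Allow a statement of no interference only if the confidence interval excludes a margin that the sponsor justifies and fixes before unblinding, saying whether it applies in one or both directions. The sponsor should know beforehand that 35 to 50 per arm gives 80% power only for margins of about 0.56 to 0.70 SD.

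Cost: a change of wording and a few extra table rows from samples already scheduled at baseline, 6 and 12 weeks. There are no new visits, blood draws or participants. The downside is a more cautious safety statement.
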